**Primary outcomes**													
	Exposure to physical hazards	3.7 (0.6)		0.5		3		18		270		0.870 (0.816-0.910)	
	Exposure to psychosocial hazards	2.4 (0.6)		0.5		3		18		270		0.870 (0.816-0.910)	
**Secondary outcomes**													
	Pain/discomfort	14.9 (8.3)		4		3		18		270		0.780 (0.753-0.805)	
	Stress	4.02 (2.56)		0.5		3		18		270		0.742 (0.714-0.768)	
	Burnout	4.76 (2.54)		0.5		3		18		270		0.734 (0.706-0.760)	
	Cognitive stress	3.33 (2.57)		0.5		3		18		270		0.745 (0.717-0.771)	

### Randomization

The exclusion criteria were applied to a complete list of “groups” of stores in the organization prior to randomization. Groups of stores were excluded where the number of eligible stores in the group fell below threshold. Figure 2 illustrates participant flow by cluster for recruitment to the study.

**Figure 2 figure2:**
[figure not shown]
Participant flow for recruitment to the study.

A list of eligible groups of 10-11 stores was provided to an independent researcher to perform randomization using a random number generator based on the stores’ numeric identifier and assign them to the control or intervention arm of the study.

A total of 3 groups of stores that met the eligibility criteria were randomly selected first, and then 6 stores were randomly selected from each of those groups. Clusters (stores) were randomly allocated to either the control or intervention arm. Pairs were not matched. Consent was not obtained at the time of recruitment and randomization of stores, as consent procedures will be followed when recruiting individual participants during data collection procedures, such as administration of the APHIRM toolkit survey or the SoC questionnaire.

### Blinding

Blinding of cluster allocations was not possible, as each cluster communicates with the other clusters in the study on a regular basis and would thus be able to determine their allocation in the study.

Raw data from the toolkit will be reviewed by a statistician on the research team who is blinded to cluster allocation.

### Statistical Methods

Baseline characteristics, including baseline values of the primary outcomes, store size (number of employees), and available aggregate demographic measures, will be summarized at the store level and presented descriptively by treatment arm (mean, SD, median, range, or proportion, as appropriate). Data for each cluster will be analyzed to identify potential outliers. Data will be cleaned and examined for normal distribution prior to analysis. The primary outcome measures (physical and psychosocial hazard severity ratings) will be analyzed by variance-weighted cluster-level ANCOVA using posttreatment store means regressed on treatment assignment and baseline store mean, with group fixed effects. Weights will be set to the inverse of the estimated theoretical variance of the cluster means to account for potential unequal cluster sizes. Because there are only 18 clusters (9 per arm) and 3 higher-level strata, estimation of higher-level variance components is unstable, and asymptotic cluster-robust SEs perform poorly. However, analyses using generalized estimating equations will be presented as sensitivity checks, with full disclosure of small-sample limitations.

Data on action plan implementation will be analyzed as categorical data. The count of actions by each status category (eg, “completed,” “in progress,” or “not started”) and categorization as “higher-order” or “lower-order” will be performed for each cluster and compared against the other outcome measures for that cluster.
Data on SoC progression will be analyzed as ordinal data. The median and mode response for the cluster will be determined as the SoC for that cluster at each measurement point. SoC data for store managers and above-store managers will be analyzed separately for each cluster. Progression through the SoC will be evaluated by assessing the number of SoC each group progresses through at each timepoint and overall, from commencement to the conclusion of the study.

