One of the 3 tools identified in the review [26] was “A Participatory Hazard Identification and Risk Management” (APHIRM) toolkit. This is a set of procedures that guides employers and workers through the 5 stages of the risk management cycle to address the sources of WMSD and MHP risk specific to a particular job. These procedures are implemented with guidance from a facilitator who has been trained to implement the toolkit. The procedures focus on implementing changes that address the sources of risks of WMSDs and MHPs. Studies evaluating the toolkit have supported its effectiveness in reducing the severity of exposure to physical and psychosocial hazards that can contribute to WMSDs and MHPs [27-29].

Effective WMSD and MHP risk reduction relies on management support, participation, and commitment of resources to implement identified actions [5,14,30,31]. Aligning approaches with management and workforce readiness for change has been suggested to improve the outcomes resulting from these changes [19,32-34]. The Stages of Change model (SoC) [35] is one approach to adapting the delivery of interventions in the workplace to the recipient’s readiness to change [32,36]. This model classifies individuals into one of five SoC: (1) precontemplation (unaware or unconcerned about workplace hazards), (2) contemplation (considering change but not yet ready to act), (3) preparation (intent to change in the near future), (4) action (made changes in the previous 6 months), and (5) maintenance (made changes and are working to consolidate gains and avoid relapse).

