### Study Objectives

To address these gaps, the aims of this research are to evaluate the impact of APHIRM toolkit implementation on hazard exposure levels for workers in the online shopping department (online department), conduct a process evaluation of the toolkit implementation in each participating work group, and evaluate the influence of SoC on the use of APHIRM toolkit resources.

To achieve these aims, this research protocol is designed to answer the following questions: does implementation of the APHIRM toolkit reduce hazard exposure levels for workers in the online department? When implementing the APHIRM toolkit, what are the key requirements to maximize its effectiveness in reducing hazard exposures for workers in the online department? Are APHIRM toolkit resources used differently when senior leaders have different SoC?

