#### Additional Outcome Measure

Managers’ SoC progression will be measured using the questionnaire included in Multimedia Appendix 1. The questionnaire will be administered every 3 months for the duration of the study via scheduled management meetings. Measurement is conducted for each relevant manager group: all the managers directly responsible for a work group in a store (online department and store managers), and managers with responsibility for groups of stores, known as “above-store managers.” Because of this, data for a manager with responsibility above a single store level may be considered when evaluating the implementation process for multiple stores under their direction, while SoC data for a store manager would only be considered in the process evaluation for the individual store under their management.

Movement through the SoC at each timepoint will be reported, as well as the absolute difference in stages, if any, from baseline to follow-up (ie, the total number of stages the work group’s managers moved through during the study period and whether movement was progressive or regressive through the SoC). This survey tool was selected as it has been previously validated as an instrument sensitive to detecting both workers’ and managers’ readiness to implement changes to address physical and psychosocial risk factors in the workplace [36,50,51]. SoC data will be collected and managed using REDCap (Research Electronic Data Capture; Vanderbilt University) electronic data capture tools hosted at La Trobe University [52,53]. REDCap is a secure, web-based software platform designed to support data capture for research studies.

A summary of outcome measures, analysis metrics, methods of aggregation, and measurement timepoints is included in Table 1.

**Table 1 table1:** Study measures, metrics, methods of aggregation, and frequency of measurement.

Primary or secondary	Outcome measure	Analysis metric	Method of aggregation	Participants providing data	Timepoints
Primary	Physical hazard measures	Change from baseline	Mean	Individual employees from each work group	At commencement and 12 months after commencement
Primary	Psychosocial hazard measures	Change from baseline	Mean	Individual employees from each work group	At commencement and 12 months after commencement
Secondary	Change in self-rated pain and discomfort	Change from baseline	Mean	Individual employees from each work group	At commencement and 12 months after commencement

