### Sample Size

Sample size calculations were based on primary outcome measures of changes in physical and psychosocial hazard severity ratings. Considerations were made to the organization’s structure when determining the number of clusters and participant numbers in each cluster. Individual stores are organized into “groups” of 10-11 stores, overseen by a group manager, justifying a 3-level cluster design.

Online department numbers were reviewed by store to determine expected cluster size. Additionally, response rates to previous surveys (not connected with the current project) were reviewed and found to be between 20% and 30%. These values were then used to calculate the sample size within each cluster to account for differences in expected recruitment across clusters. The mean cluster size (number of expected participants in a cluster) was set at 15, with a cluster variation of 0.7. If the mean cluster size deviates significantly from the estimated value of 15, this will be identified and accounted for in the statistical analysis and the interpretation of results.

Table 2 sets out the sample size and power calculations for primary and secondary outcomes evaluated in the randomized controlled trial, taking into account the 3-level cluster design at α=.05, intraclass correlation coefficient level 2=0.10; intraclass correlation coefficient level 3=0.05, mean cluster size=15; and estimated cluster variation=0.7, derived using Monte Carlo simulation. A previous study was used to estimate the effect size for exposure to physical hazards, exposure to psychosocial hazards, and self-rated pain and discomfort scores [55]. Results from Rahimi [56] were used to estimate effect sizes for stress scores.

On this basis, it was determined that 9 control and 9 intervention clusters (18 clusters in total) were required to achieve power of 0.8 or more.

**Table 2 table2:** Sample size and power calculations.

Outcome			Mean (SD)		Effect size (*d*)		Groups (level 3), count		Stores (level 2), count		Employees (level 1), approximate n		Power (95% CI)

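### A store's stage of change is defined as both the median and the mode, and above-store managers are analysed per store although about three of them cover all 18 stores

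*Protocol article*

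**What the plan says.** All references are to the protocol article.

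- **Scale.** The Background describes five ordered stages: "This model classifies individuals into one of five SoC".
- **Store-level respondents.** The Additional Outcome Measure section includes "all the managers directly responsible for a work group in a store (online department and store managers"). It does not say how many people that is per store.
- **Store value.** Statistical Methods: "The median and mode response for the cluster will be determined as the SoC for that cluster at each measurement point". Progression is then the number of stages moved at each timepoint and overall.
- **Two tiers of manager.** Statistical Methods: "SoC data for store managers and above-store managers will be analyzed separately for each cluster". The Trial Design section defines a cluster as one store's online department.
- **Who is above the store.** The Sample Size section says that stores sit in groups of 10-11, "overseen by a group manager, justifying a 3-level cluster design".
- **Selection and allocation.** In Randomization, three groups were drawn, then "6 stores were randomly selected from each of those groups", and "Clusters (stores) were randomly allocated to either the control or intervention arm. Pairs were not matched".
- **Use of the variable.** The third research question is "Are APHIRM toolkit resources used differently when senior leaders have different SoC". The Process Evaluation section relates toolkit use to the cluster's SoC.
- **Rank.** Table 1 lists SoC progression as an additional outcome, below the primary and secondary ones.

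**The concern.** There are two separate problems.

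First, the median and the mode of a few ordinal responses need not agree, and the mode need not be unique. The smallest store team that fits the description, one online department manager and one store manager, is the worst case: whenever the two differ there is no unique mode, and when their stages differ by an odd number the median falls between stages. The planned metric counts stages moved, so it needs one stage per store at each timepoint. An analyst would have to choose a rule after seeing the data.

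Second, a group manager's SoC varies between groups, not between stores. Analysed for each cluster, one response is repeated for up to six stores. A table with 18 store rows, or 9 for toolkit use in the intervention stores, would suggest far more information than exists. If senior leaders in the third research question means above-store managers, the evidence on that question is limited by the number of those managers.

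**Working it through.** The protocol gives no sample size or power for SoC, so there is no figure of its own to reproduce. The design count agrees: 3 groups x 6 stores = 18 stores, 9 per arm.

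**1. How often do median and mode fail to give one stage?**

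Neither the number of managers per store nor the spread of stages is given, so both are assumed. Managers are taken as independent, with these probabilities for stages 1 to 5:

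- A, uniform: 20/20/20/20/20%
- B, moderate: 5/15/30/40/10%
- C, concentrated: 2/8/15/70/5%

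With two managers the rule fails whenever they differ: P = 1 - sum of p_i squared.

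- A: 1 - 5 x 0.04 = 0.80
- B: 1 - (0.0025 + 0.0225 + 0.09 + 0.16 + 0.01) = 0.715
- C: 1 - (0.0004 + 0.0064 + 0.0225 + 0.49 + 0.0025) = 0.478

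The median is a half-stage when one manager is at an odd stage and the other at an even one: P = 2 x P(odd) x P(even).

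- A: 2 x 0.60 x 0.40 = 0.48
- B: 2 x 0.45 x 0.55 = 0.495
- C: 2 x 0.22 x 0.78 = 0.343

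Full enumeration of response patterns gives the share of store-timepoints with no single stage that is both median and unique mode:

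| Managers per store | A | B | C |
|---|---|---|---|
| 1 | 0% | 0% | 0% |
| 2 | 80% | 71.5% | 47.8% |
| 3 | 48% | 33.6% | 12.9% |
| 4 | 67.2% | 50.6% | 23.9% |

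**2. Are above-store managers shared across arms?**

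Nine stores per arm cannot be made up of whole groups of six, so at least one group must contain both arms. The text does not say that allocation was balanced within groups. If it was an unrestricted 9:9 draw:

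- Possible allocations: C(18,9) = 48,620.
- With at least one single-arm group: 6 x C(12,3) - 6 x C(6,3) = 1,320 - 120 = 1,200.
- P(all three groups mixed) = 1 - 1,200/48,620 = 97.5%.
- P(exactly 3:3 in every group) = 20 x 20 x 20/48,620 = 16.5%.

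**3. What would a per-store arm contrast of above-store SoC show?**

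Assume one manager per group and, for illustration, progressions of 2, 1 and 0 stages, copied to the six stores of each group:

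| Intervention stores per group | Intervention mean | Control mean |
|---|---|---|
| 3, 3, 3 | 9/9 = 1.00 | 9/9 = 1.00 |
| 4, 3, 2 | 11/9 = 1.22 | 7/9 = 0.78 |
| 5, 3, 1 | 13/9 = 1.44 | 5/9 = 0.56 |

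At 3:3 in every group the difference is zero whatever the managers answer. Otherwise it reflects only how the groups fell between arms. In neither case does it carry information about treatment.

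**The case against.** **No arm comparison is planned.** A reader might infer that the trial compares SoC between arms and that the above-store result is null by construction. The documents do not support this. The comparison of the two arms is written for the primary outcomes; for SoC only movement through the stages is reported. Control-store managers do complete the questionnaire, and Figure 1 is introduced as showing comparison data, but no SoC contrast or test is named. A zero difference in store means would also be forced only by a 3:3 split in every group, which is not stated. Store-level managers belong to one store, so their results are not affected. This part of the objection stands in full.

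**The sharing is disclosed.** The Additional Outcome Measure section says that an above-store manager's data may be used for several stores in the process evaluation, and the two tiers are kept apart. That is fair, and nowhere does the protocol claim 18 independent values. But the disclosure does not change the stated unit of analysis, which remains the store.

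**The third research question has no test.** It draws on facilitators' observations, with no power claimed, so a descriptive answer is close to what is planned. This stands. What is missing is the number of managers on which that answer rests.

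**The percentages are assumed.** This stands too. Managers of one store may well answer alike, and with a single respondent the rule always works, as it would for a lone group manager. The figures are a range, not a forecast.

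**Tie rules belong in an analysis plan.** A rule for half-stages could. But the protocol does not leave the matter open: it states a rule, and that rule assigns two statistics to one value.

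**Conclusion.** The point holds, as a minor one. The store-level rule does not yield a single stage whenever two managers of a store differ. Its failure rate is about 48-80% of store-timepoints with two managers, 13-48% with three and nil with one, under the assumed distributions and independent answers. The defect itself rests on the wording alone and needs none of these figures.

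The above-store SoC is placed at the wrong unit. Assuming one manager per group, there are about 3 independent values behind 18 stores, or behind the 9 intervention stores where toolkit use is observed. That at least one group spans both arms follows from the counts; that all three do is 97.5% likely under unrestricted allocation, and is an inference. Any arm contrast of this measure would be uninformative, but none is specified, so this is a caution and not an error in a planned analysis.

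No primary or secondary outcome is affected.

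**What to change.** - **Store level.** Report each store-level manager's own stage and transitions. If one value per store is needed, use the median, with a rule for half-stages set before the data are viewed, and drop the mode. A half-stage rule is needed even with the median alone: with two managers a half-stage arises in 34-49.5% of store-timepoints under the assumptions above.
- **Above-store level.** Analyse each above-store manager once, descriptively and without an arm contrast. State how many such managers there are and which stores in which arm each oversees.
- **Third research question.** Say whether senior leaders means above-store managers. If so, state that the answer is descriptive and rests on that number of managers, not on the number of stores.

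The cost is wording only; no extra data are needed. The protocol reports that the data had not been viewed as of January 2026, so the rule can still be set without knowledge of the results. The downside is that the above-store result is openly labelled descriptive.

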### Missing Data

The APHIRM toolkit survey requires completion of each item before the next one is presented, so a missing data strategy is not required. The SoC questionnaire is also managed in the same way. Consequently, a plan for handling missing data with respect to these data is not required.

Facilitators submit a completed worksheet at the end of each session completed with each cluster. This is used to evaluate adherence to protocol and to investigate and document any deviations from the protocol. These will be documented in the records maintained for each cluster, which are used to complete the process evaluation for this study.

## Results

Funding for the study was approved in June 2025. Ethics approval for the study was granted in July 2025. Recruitment and randomization commenced in August 2025. This included identification of eligible stores and randomization of the eligible stores to the control or intervention groups until the required sample size was achieved. Data collection commenced in September 2025. These timings resulted from a necessary operational requirement to avoid key study activities coinciding with busy trading periods, such as Christmas and Easter, without delaying the commencement of the study. As of January 2026, a total of 18 stores were recruited to the study, with 332 individuals responding to the APHIRM toolkit survey. Response rates to the APHIRM toolkit survey for each cluster range between 28% and 85%, with an average response rate of 47% of all eligible employees. Data have not been viewed by the research team. The intervention is expected to conclude in September 2026, and results are anticipated to be published in early 2028.

## Discussion

### Generalizability

WMSDs and MHPs have a significant impact on Australian workers and workplaces, including the retail trade sector [57]. Recommendations from research on WMSD and MHP prevention advocate for a participatory approach, focusing on the whole job rather than discrete tasks, and taking into account both physical and psychosocial hazards [18,58,59]. Previous research has highlighted the evidence-to-practice gap in prevention practices, including those used by safety professionals in the retail sector [5]. This study aims to translate research evidence into practice and address WMSD and MHP hazards through implementation of the APHIRM toolkit. This study seeks to understand what support managers and decision makers require to facilitate effective implementation of these practices in their area of control. This is an important evidence gap in understanding the manager’s role in successful workplace interventions [36,41,60]. It is anticipated that these findings could be used to recommend future improvements to the design and content of supporting resources in the APHIRM toolkit.

The retail organization hosting this study is one of Australia’s largest employers, with more than 1100 locations across the country. This provides an opportunity to examine the study’s research questions at a level of organizational scale and complexity that is often not possible in Australia. The design also provides an opportunity to understand how to support large, multisite employers to bridge the evidence-to-practice gap with respect to WMSD and MHP risk management. This is important for employers, who, due to organizational size, complexity, and geographic spread, must rely on nonexperts to implement and maintain risk management practices with respect to WMSD and MHP prevention. The design of the study endeavors to replicate real-world conditions of toolkit implementation as closely as possible so that findings can be generalized to other work groups in the organization as much as possible. However, the availability of staff in the organization to act as facilitators, and their location—proximal to state capital cities—may present a limitation to the generalizability of findings to regional and remote work group locations.

As part of identifying recommendations to improve these practices, this study provides an opportunity to understand how managers at different levels of a large organization, and in different physical locations, progress through SoC during implementation of the APHIRM toolkit. The study also presents an opportunity to understand how managers’ progression through SoC relates to outcomes from toolkit implementation. It is anticipated that this study could also inform how the APHIRM toolkit could be best used, and possibly adapted, for use in large multisite organizations, in ways that support managers of work groups at different SoC. The intervention strategy aims to replicate how the toolkit may be implemented within a large organization, which serves to build the capacity of individual stores, their leadership teams, and their supporting safety professionals to more effectively manage the risks of WMSDs and MHPs. It is anticipated that the findings of the study could be applied to other large, multisite organizations, particularly in the Australian retail sector.

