An individual’s SoC is determined by their current knowledge, attitudes, and beliefs regarding the issue in focus. The key constructs thought to influence movement through the stages are decisional balance, that is, weighing the pros and cons of changing, and habit strength, that is, the ability to sustain a target behavior over time [37,38]. A scoping review [39] identified few intervention studies performed in a workplace setting that used the SoC model. Previous studies on WMSD prevention [36,40,41] have used the SoC model to evaluate whether advice and interventions tailored to the target’s SoC are more effective at addressing WMSD hazards in the workplace. In this earlier work, both the managers’ and employees’ SoC were evaluated simultaneously, using a short questionnaire. Those in earlier SoC made a greater number of successful ergonomics changes when advice was tailored to their SoC. This suggests that such an approach has promise for improving the effectiveness of interventions aimed at making ergonomics changes in the workplace. Less attention has been paid specifically to the relationship between managers’ or decision-makers’ SoC (as a proxy for readiness to make changes) and the success of ergonomics interventions implemented in their area of control [19,31,36].

There is an opportunity to implement the APHIRM toolkit in a large retail organization and assess its impact on WMSD and MHP hazard exposure. The process evaluation conducted in this study will inform more effective toolkit implementation in organizations of similar scale and/or risk profile, accounting for managers’ SoC. Implementation science methodologies have been recommended as an approach to a process evaluation [26,42,43], to improve robustness, while maintaining a “real-world” context. This study intends to build on available evidence relating to effective WMSD and MHP risk management obtained from previous workplace-based studies, particularly those which have implemented the APHIRM toolkit. There are few published studies that describe the implementation of the APHIRM toolkit in large workplaces [44,45].

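### Managers' stage progression overlaps in part with the action-implementation outcome, runs concurrently with the other outcomes and is capped by starting stage, so its association with outcomes cannot be read as an influence of readiness

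*Protocol article*

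**What the plan says.** - **Stage definitions (Introduction, Background).** The first three stages describe awareness, consideration and intent; the third is "3) preparation (intent to change in the near future". The last two describe changes made: "action (made changes in the previous 6 months" and "5) maintenance (made changes and are working to consolidate gains and avoid relapse".
- **Construct.** The same section takes managers' SoC "as a proxy for readiness to make changes".
- **Aim (Study Objectives).** The SoC aim is to "evaluate the influence of SoC on the use of APHIRM toolkit resources". The matching research question asks about leaders at different stages.
- **Metric (Additional Outcome Measure; Table 1; Statistical Methods).** SoC is read at commencement and every 3 months. "Progression through the SoC will be evaluated by assessing the number of SoC each group progresses through at each timepoint and overall". The stage of a cluster is the median and mode over its managers, with store and above-store managers kept apart.
- **Action outcome (Action Plan Implementation; Table 1).** Actions are classed by completion status through the toolkit portal and counted per cluster at 12 months.
- **Cross-comparison (Statistical Methods).** Action counts are to be set against the cluster's other outcome measures. SoC progression is listed as an additional outcome measure, so this comparison can include it.
- **Intended reading.** The Generalizability section hopes to learn how "progression through SoC relates to outcomes from toolkit implementation". The Abstract's conclusions speak of SoC possibly influencing outcomes and of informing the tailoring of interventions to SoC.

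**The concern.** Readiness comes before change, whereas stages 4 and 5 record that change has happened. The intervention consists of making changes: monthly sessions build and carry out an action plan in departments run by the managers whose stage is being read. A manager may thus move up the scale because the plan was carried out, and the move then appears as a correlate of implementation.

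For hazard severity, pain and stress the difficulty is timing. Progression accrues over the same 12 months as the change in these scores, so the outcome may drive the stage, or one cause may drive both.

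The count of stages also depends on the starting point. A store whose managers begin at stage 4 or 5 has little or no room to progress, however well it implements.

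At stake is one of the article's intended lessons. A positive association could be taken as support for tailoring interventions to SoC when readiness had no part in it, while the ceiling could make the readiest stores look like non-progressors. The Limitations section mentions neither the overlap nor the direction of effect.

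**Working it through.** The article gives no figure for this point, so there is none to reproduce. The check sets the definitions beside the metric, works out the ceiling, and then illustrates the possible size.

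**1. Where progression and outcomes coincide**

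| Outcome | Source | Relation to stage progression |
|---|---|---|
| Action counts | Risk management teams, portal | Entry to stages 4-5 overlaps in concept (changes made), same period |
| Hazard severity, pain, stress | Workers' survey, baseline and 12 months | Separate measures; concurrent, so reverse or shared causation is possible |
| Use of toolkit resources | Facilitators' session notes | Separate; the stated question concerns stage, not stages gained |

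Movement within stages 1-3 involves no changes made and remains information about readiness.

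**2. Ceiling**

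Maximum gain = 5 − starting stage. Gain on reaching stage 4 = 4 − starting stage.

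| Starting stage | Gain on reaching stage 4 | Maximum gain |
|---|---|---|
| 1 | 4 − 1 = 3 | 5 − 1 = 4 |
| 2 | 4 − 2 = 2 | 5 − 2 = 3 |
| 3 | 4 − 3 = 1 | 5 − 3 = 2 |
| 4 | 0 | 5 − 4 = 1 |
| 5 | not applicable | 5 − 5 = 0 |

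Stores that end at the same stage can therefore score anything from 0 to 3, according to where they began.

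**3. Illustration when readiness has no effect**

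Only the 9 intervention stores come from the article. Every other input is an assumption:

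- completed actions per store are gamma-Poisson with mean 2;
- starting stage is 1, 2 or 3, independent of actions;
- in a share s of stores the final stage follows the definition (two or more completed actions gives stage 4, otherwise no move), and the remaining stores move 0 or 1 stage at random;
- the correlation of actions with hazard change is set at 0, 0.3 or 0.6.

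The measure is Spearman's correlation, with 1,500 runs per setting. The 5% cut-off for n = 9 uses t = 2.365 on 7 degrees of freedom: r = t/√(7 + t²) = 2.365/√12.59 = 0.666.

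| | s = 0 | s = 0.5 | s = 1 |
|---|---|---|---|
| Progression vs action count, mean correlation | about 0 | 0.47 | 0.79 |
| Share of runs beyond ±0.666 | 5-6% | 27-28% | 85-87% |
| Progression vs hazard change, mean correlation (strength 0 / 0.3 / 0.6) | about 0 throughout | 0 / 0.11 / 0.23 | 0 / 0.20 / 0.38 |
| Commencement stage vs action count, mean correlation | about 0 | about 0 | about 0 |

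If stage follows changes made, a sizeable progression-action correlation arises without any readiness effect. The spill-over to hazard change is weaker and indirect. Commencement stage shows no such artefact.

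**The case against.** The strongest reply is that the article fixes no such test. The Generalizability sentence describes an opportunity, the planned SoC analysis is descriptive, and the formal question in Study Objectives concerns stage and resource use, which the overlap does not reach. All of this stands, and it limits the weight of the point. It does not remove it: the article fixes the metric as stages moved, provides for a comparison of action counts with the other outcomes, and speaks of SoC influencing outcomes.

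A second reply is that time order and starting stage can be recovered, because SoC is read every 3 months, action status is reviewed monthly, and movement is reported at each timepoint with its direction. That is correct, and it is why the remedy is cheap. The plan does not, however, say that these readings will be used in that way.

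A reader might go further and infer that relating progression to toolkit outcomes merely correlates implemented actions with themselves. The documents do not support this. Hazard severity, pain and stress are rated by workers and are not actions. Action counts come from the portal, with independent review by the research team, while SoC comes from a manager questionnaire described as validated for readiness.

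A reader might also infer that one completed action moves a manager to stage 4 automatically. That cannot be checked: the questionnaire is in an appendix that is not shown, the Background ties stage to knowledge, attitudes and beliefs, and cluster stage is a median and mode, so one manager's move need not shift it.

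**Conclusion.** The point holds as a limit on interpretation. By the article's own definitions, moving into stages 4-5 overlaps in part with the action-implementation outcome. Progression is concurrent with the remaining outcomes, and it is capped at +1 from stage 4 and 0 from stage 5. An association between progression and outcomes therefore cannot be read as readiness influencing outcomes.

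The overlap and the ceiling follow from the stage definitions and the metric. The size does not: correlations of 0.47 to 0.79 rest wholly on assumed inputs, and they fall to about 0 if the questionnaire's staging is unrelated to changes made. The point is minor to moderate. It concerns an additional, exploratory outcome and leaves the primary ANCOVA untouched.

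**What to change.** 1. For any question about the influence of SoC, use the commencement stage as the explanatory variable for later resource use, action completion and hazard change. For resource use and action completion, which are recorded at the monthly sessions, the preceding 3-monthly reading may serve instead, counting only what follows that reading. For hazard change from baseline to 12 months, the commencement reading is the cleaner choice, since later readings fall within the period of change.
2. Report progression as an outcome, by starting stage, with movement within stages 1-3 shown separately from entry to stages 4-5.
3. Present progression against completed-action counts as descriptive only, and state in the Limitations that it does not show an effect of readiness.

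Even a time-ordered association across 9 intervention stores remains exploratory and open to confounding, and should be described so.

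The cost is analysis wording and a little more tabulation. Both the commencement and the 3-monthly readings are already scheduled, and the Results section states that the research team had not viewed the data as of January 2026, so the change can still be made before results are known.
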